**1.0 OUTLINE OF THE PRESENT STUDY**

Among men who have sex with men (MSM) in Ontario, from 2001 to 2006, HIV diagnoses increased 26%1. In 2006, there were 522 new cases of HIV among MSM, and MSM accounted for 65.2% of HIV of new cases in Ontario (including 2.8% who are MSM and injection drug users). An estimated 19.6% of Toronto MSM are HIV-positive (HIV+)2. Behavioural trends in the same time period show that seroconversions are not randomly distributed across the population of gay and bisexual men. Unprotected anal intercourse (UAI) appears to occur more frequently among HIV+ versus HIV-negative MSM. For example, in a study of HIV+ MSM recruited in both 2005 and 2007, 37.6% of MSM had engaged in UAI with partners of unknown or serodiscordant HIV status, as opposed to 13.3% of HIV-negative MSM3. Among both HIV+ and HIV-negative men, half of all the unprotected sex reported in the previous six months occurred among those who identified themselves as participants in the “bareback scene” or “bareback websites” (i.e. venues facilitating intentional UAI)4,5.

Despite continued UAI among HIV+ persons, the vast majority of prevention efforts have focused on HIV-negative populations. Further, few intervention studies to our knowledge have specifically examined the effects of an intervention intended for HIV+ MSM. However, given the potentially greater impact on the HIV epidemic of decreasing sexual risk behaviour of HIV+ persons, it is critical that these interventions be developed for HIV+ MSM, and that these interventions acknowledge the recent effect of barebacking-related beliefs among certain groups of MSM6.

The primary objective of the present study is to determine the effect size of a theoretically-guided HIV prevention program for HIV+ MSM to reduce HIV transmission risk behaviour using a community-based research framework. An effective HIV prevention intervention for HIV+ MSM has the potential to make a significant difference in epidemiological trends, given the high HIV prevalence rate among MSM in Canada and increasing HIV incidence. An effective intervention also may have wider health benefits for HIV+ men by reducing exposure to co-infection with hepatitis, Lymphogranuloma venereum, syphilis, and other sexually transmitted infections (STIs), and with alternative strains of HIV7,8.

**2.0 BACKGROUND AND RATIONALE**

**2.1 UAI with HIV-negative or unknown serostatus partners among HIV+ MSM**

Several studies suggest that many MSM operate under mistaken assumptions about their sexual partners’ HIV status. Many HIV+ men read the willingness of their partners to engage in UAI as itself evidence that partners are already HIV+9-18. HIV-negative men, on the other hand, may assume the opposite: that partners willing to engage in UAI “must be” negative19,20. However, these assumptions may frequently be mistaken, as 64% of partners of HIV+ persons who were perceived by participants as HIV+ were actually HIV-negative11.

Another important factor that may account for the increasing HIV prevalence among MSM in Ontario is the rise of barebacking, often defined as intentional UAI4,22. The development of sub-groups of men who bareback among HIV+ men may account for a cascade of recent evidence showing elevated and rising rates of UAI among HIV+ men with partners of unknown or negative HIV status23-37. The Ontario Men’s Survey38 found that 30% of HIV+ men reported having UAI with a partner of unknown serostatus during the previous year, and 20% with a partner they assumed to be HIV-negative. It is critical to note that while most (but not all) barebackers are HIV+, most HIV+ men are not barebackers39. Many practise safe sex and many more employ risk reduction techniques if a condom is not used. However, there is still an unmet need for empirically tested interventions to reduce sexual risk behaviour among HIV+ MSM, including those who engage in barebacking (intentional UAI) with non-HIV+ partners or who otherwise engage in UAI with non-HIV+ partners without a previous intention of engaging in UAI.

**2.2 Interventions to reduce sexual risk behaviour among HIV+ persons and MSM**

The most recent meta-analyses suggest that behavioural interventions are efficacious at reducing self-reported UAI among MSM (RR = 0.80, 95% CI 0.72-0.89)40. Among small group and individual-level interventions, significant effects were observed for interventions that addressed information, risk perception, self-efficacy, personal skills (e.g., self-reinforcement for behaviour change) and interpersonal skills related to sex. Effects found in multivariate analyses were observed for interventions that addressed perceptions of risk and losses, such as unprotected sex can harm you, versus those that addressed only gains from safer sex. Interventions were not differentially effective whether an intervention was delivered by peers versus others, or individual versus small-group based. Given that interventions outside the United States demonstrated a nonsignificant reduction in UAI41, and especially given the lack of efficacious interventions designed for Canadian populations of people living with HIV, there is a specific need for research investigating the effects of behavioural interventions in Canada.

Other reviews have found42 greater efficacy with more active interventions (i.e., participants role-play problem situations, or practice applying condoms to a model) rather than passive interventions where participants just receive information. An efficacious intervention among HIV+ persons43 used scenes drawn from films, plus active role playing, in a program delivered to primarily African American HIV+ men and women, both gay and straight, in: (1) developing skills to cope with HIV-related stressors and sexual risk producing situations, (2) enhancing decision-making skills for self-disclosing HIV serostatus to sexual partners, and (3) facilitating the development and maintenance of safer sexual practices. Other interventions report variations on this model focussing on improving self-efficacy in negotiating safer sex and/or disclosure skills 44-49.

There have been far fewer behavioural interventions specifically focusing on reducing HIV transmission risk behaviour among HIV+ MSM. The relative lack of behavioural interventions for HIV+ MSM is problematic because behavioural interventions including samples with more than 35% HIV+ MSM were not efficacious in a recent meta-analysis41. Another40 meta-analysis of the positive prevention literature reported that interventions were efficacious to the extent that they did not focus on HIV+ MSM. In one of the largest and most intensive interventions developed to date, the Seropositive Urban Men’s Intervention Trial (SUMIT) found that participants had less receptive UAI after the 6-week course, but the effect faded 3 months later50. The SUMIT investigators speculated that SUMIT’s lack of efficacy may have been due to the influence of some participants in small group discussions who “disclosed that they regularly had unprotected sex, that they believed that their partners should be responsible for their own health, and that they were not convinced that they could transmit HIV during receptive anal or insertive oral sex”. This is particularly noteworthy as these views are recognizable as central tenets of the bareback sub-group of MSM.

In summary, from previous intervention research and our own interviews with Toronto MSM having UAI most or all of the time6, it appears that it is necessary to engage the emerging culture of risky sex among HIV+ MSM if the incidence of UAI, especially with partners of negative or unknown serostatus, is to be reduced. The present study will address this challenge in Canada by engaging HIV+ MSM in a community setting and employing an empirically supported model, the Information-Motivation-Behavioral Skills51,52 focusing on information, motivation, and behaviour skills as a means to prevent HIV transmission risk behaviour. The IMB model will be delivered by motivational enhancement counseling (also known as “motivational interviewing”), a counseling technique that that expresses empathy for the participants, highlights differences between current behaviour and current health promotion goals, avoids argumentation with clients, and supports a participant’s self-confidence in his ability to engage in risk reduction behaviours53-56.

**2.3 Guiding Model for the Intervention: The IMB Model**

**2.3.1 Elicitation research using the IMB model**. The IMB model developed by Fisher et al. (2002) will serve as the theoretical model guiding the present study’s HIV prevention intervention52. This behavioural model, supported by PHAC’s Canadian Guidelines for Sexual Health Education57, is strongly empirically supported for a variety of populations regarding HIV risk prediction and in the development of efficacious HIV prevention interventions23,58-62. The IMB model specifies that HIV prevention information and motivation are relatively independent constructs which increase HIV preventive behaviour directly and by increasing behavioural skills (e.g. effective condom negotiation) that in turn increase HIV preventive behaviour. The IMB model specifies that elicitation research must first be conducted before designing HIV prevention interventions. Elicitation research refers to research that identifies relevant information, motivation, and behavioural skills of the target population, and typically includes focus groups, interviews, and surveys. This research has already been conducted by the study team on the information, motivation, and behavioural skills of HIV+ MSM in Ontario4,14,15 and is reviewed below:

**2.3.2 Information.** This is a population that is largely well-informed about the basics of HIV transmission and pathogenesi**s**59 and typically already in treatment. Based on our own research4, as well as that of others, HIV+ men need advanced information that could help them in their decision making processes regarding HIV risk, including: 1) the relationship between viral load and transmission59, 2) solutions to erectile problems10,63,64, 3) unprotected sex and acquisition of alternative strains of HIV, syphilis, LGV, hepatitis C, etc, 4) the risk of top or bottom roles in sex and the risk of sex with another HIV+ person4, 5) risks of presuming or intuiting a potential partner’s sero-status, and 6) the current legal context in Canada in which unprotected sex without disclosure may be considered a crime65.

**2.3.3 Motivation**. For this set of men who have unprotected sex much of the time, motivation is a critically important area to address. Men with bareback practices demonstrate inconsistent motivations regarding engaging in unprotected anal intercourse. For example, although they fairly consistently engage in UAI and are aware of risk of HIV transmission, few, if any, wish transmission to occur and most, if not all, articulate their desire to actively avoid transmission. Many also express a desire to give back to the gay community and to protect younger or uninformed men14.

**2.3.4 Behavioural skills.** While the central focus for risk reduction will be on condom use in anal intercourse, research documents the complex array of behaviours and skills required for consistent condom use47-49, 58. Based on the extant literature, it is anticipated that this intervention will address: (a) HIV-status disclosure skills; (b) negotiation of safer sex practices; (c) exploration of nonpenetrative sex alternatives; and (d) experimentation with a variety of condoms to enhance the condom-wearing experience, in a context of expanding ideas of what may be desirable and how to have sexy, satisfying, and intimate relations. Behavioural skills are typically delivered using both role play of behavioural skills and identification of high-risk situations (e.g. substance use, depression). Behavioural skills approaches can be integrated into motivational approaches to create efficacious interventions, and have been used in previous studies with heterosexual populations58.

**2.4 Intervention Implementation**

**2.4.1 The Intervention Implementation Model: Motivational Enhancement Counselling**

Per the IMB model, the study intervention will specifically address HIV prevention information, motivation, and behavioural skills. The intervention implementation model, will build directly from the IMB theoretical model using motivational enhancement counselling53,55,58,59. Motivational enhancement counselling is designed to induce rapid, internally motivated change by using the participants’ own change resources58,60. The specific steps include: 1) eliciting from the participant his ideas about how a behaviour can be changed, 2) enhancing the participant’s confidence in being able to make the desired change, while 3) constantly attempting to help the participant locate and express his own reasons for wanting to change53. Motivational enhancement counselling also tailors the intervention toward a participant’s stage of readiness to make change54,66. Considering the recurrence of social isolation as a theme in the narratives of risk-taking men38,53,68-70, the intervention will also be designed as a small group counselling session to help foster social interaction among participants. A major difference between the small group intervention for HIV+ MSM described by Wolitski et al (2004) and the small group intervention in the current study is the intervention implementation model. The unsuccessful SUMIT intervention used social cognitive theory, which posits that people make change when given sufficient information and behavioural skills68,71,72. In contrast, the intervention in the present study does not assume that information and behavioural skills are sufficient to make change, and instead relies also on helping participants to find their own internal motivations to engage in behavioural change. Motivational enhancement counselling is also a goal-directed counselling style that has been shown to be effective in reducing sexual transmission risk behaviour for primarily HIV-negative samples of MSM and high-risk heterosexuals60,62.

Informational component. In this component of the intervention, delivered primarily in Sessions 1 and 2, facilitators will review information about transmissibility of HIV and its association with HIV viral load and medical factors, discussion of other STIs and their effects on HIV disease, and strategies used by MSM to promote sexual health, and psychosocial problems that decrease sexual health. This component will use interactive activities to dispute myths about HIV (e.g., “Unprotected sex is not risky if you are already HIV+”) and to discuss risk which behaviours are of greater or lesser risk for HIV transmission.

Motivational component. Key to this approach is identification of areas of inconsistent or conflicting motivations. Working with participants’ own sometimes inconsistent beliefs, for example, that partners are (solely) responsible for HIV risk, but at the same time, expressing altruistic values of taking care of other gay men and contributing to gay community, offers significant starting points for carrying forward the techniques of motivational enhancement counselling. This component will be delivered primarily in sessions 2-6.

Behavioural skills component. In sessions 4-6, the facilitators will help participants manage cues that may serve as triggers for risky sexual behaviour, and to identify strategies to reduce their risk of contracting STIs and/or transmitting HIV. This component will include role-play exercises of risk-reduction skills, and will use the knowledge of the group to help individual group members to begin and maintain behavioural change.

It should be noted that although there are three different components of the intervention, the components are interlaced throughout the intervention, albeit at different amounts. For example, per motivational enhancement counselling, information provision is more appropriate at earlier stages of readiness for change53,54, and behavioural skills are more appropriate once intrinsic motivation is increased to a level in which the participant is ready to make behavioural changes.

**2.4.2 Structure of the Intervention**

The intervention will take the form of a small counselling group, since this is one of the most common intervention forms for similar populations. Recent studies have found positive effects on cardiovascular health behaviours (e.g., exercise, diet) using motivational enhancement counselling in a small group-forma**t73.** Participants will be organized into 7 groups of approximately 6 participants, each of which will be led by 2 facilitators who are HIV+ MSM. Months 1-4 will be spent completing the final version of the intervention manual, based upon data that will be received through focus groups with HIV+ MSM and with prevention and care providers for HIV+ MSM. These data come from the preliminary one-year project received by our team and will be completely analyzed by March 2009 and ready for incorporation into the manual. Per the IMB theoretical model and the motivational enhancement counselling treatment model, an outline of this manual has already been created and is found in Appendix 1.

**3.0 PRINCIPAL AIMS AND HYPOTHESIS OF THE PRESENT STUDY**

The current study will investigate an HIV prevention intervention for HIV+ MSM. This Phase II trial will determine the effect size of the intervention, while incorporating one aspect of a Phase I trial by examining the tolerability of the intervention among HIV+ MSM. The present study is intended to be a rigorous evaluation of the HIV prevention intervention, with the ultimate aim of evaluating the efficacy of the intervention using a Phase III randomized control trial (RCT), per standard procedures for evaluating health interventions74**.**

The study hypothesis is that the study intervention will result in reduced prevalence of unprotected anal intercourse (UAI) with partners who are HIV-negative or unknown serostatus.

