**4.2 Overview of the Study Design**

Written informed consent will be obtained prior to study enrolment including permission to complete study measures. Those who agree to enrol and meet inclusion criteria will be scheduled for a single assessment session to complete a demographics questionnaire, self-report measures, and a brief interview. Participants will complete 6 sessions of a small-group sexual health intervention to reduce sexual risk behaviour. Assessments will be conducted at the completion of each 6-session group, with follow-up assessments conducted at post-intervention and at 3 months following the end of each group.

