**4.3 Sample**

Individuals will be eligible to participate in the intervention if they: (1) are HIV+ men who report UAI with a partner of HIV-negative or unknown HIV status in the past 3 months; (2) speak and understand English, (2) anticipate that they will be able to attend all workshops; and (3) are willing to participate in program monitoring and evaluation. Persons will be excluded if it is found that their ability to respond to study measures could be compromised by 1) central nervous system conditions (e.g., advanced HIV-associated dementia), 2) acute psychotic conditions, 3) acute mood dysregulation (e.g., manic states), and/or 4) debilitating physical conditions. For ethical reasons, all participants may withdraw from the research component of the study while still remaining in the intervention. Based on the literature, we anticipate that a number of participants will display psychological or other lifestyle characteristics that are strongly associated with sexual risk taking. They will be offered referral to counselling where appropriate; however, the decision to pursue such additional support will be left with the individual men and will not influence their eligibility to participate in the intervention. To avoid conflict of interest, participants who are given referrals will be referred to counselling with providers outside the study team. In addition, if a participant experiences distress at any time, referrals for counselling will be ready at hand. Intervention program facilitators will be trained in group facilitation and will be knowledgeable about referral sources for HIV+ group members who seek information or counselling, and the project will be housed at the AIDS Committee of Toronto which has HIV-related counselling and information resources.

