**4.5 Recruitment**

Our recent findings suggest that about half of HIV+ men are likely to have had unprotected sex with a partner who is HIV- or of unknown sero-status75. Recruitment will be done from a clustering of venues, identified in our research, where men who have unprotected sex most or all of the time are over-represented4. Our team has found these venues to be accessible and their participants to be interested in participation in research. We do not expect HIV+ MSM to be attracted to workshops billed as being only about HIV prevention, but rather to a program with a larger sexual health agenda developed through our previous studies. We will seek, where possible, to encourage the participation of men with diverse ethno-cultural backgrounds and will call on the experience of research team and PPWG members who are themselves HIV+ members of Asian, Latin American, and Caribbean communities to assist in this process.

Advertisements will be placed in newspapers and magazines serving the gay community (e.g., *Fab, Xtra*) and PHAs (e.g., *The Positive Side*). Flyers about the study will also be given for distribution by AIDS Service Organizations, such as the AIDS Committee of Toronto and ethnoracial-specific AIDS service organizations (e.g., African and Caribbean Council on HIV/AIDS members, Alliance for South Asian AIDS Prevention, Asian Community AIDS Services) in the Greater Toronto Area. All study flyers and advertisements will describe the nature of the study and will provide the phone number and email of the study coordinator. Interested participants will be invited to come to the study office in downtown Toronto to learn more. Both the study coordinator and our two HIV+ gay male facilitators will conduct recruitment. In this setting, participants will have an opportunity to ask questions and receive additional explanation before signing a consent form. The consent form will include an explanation of the study, risks and benefits of participation, the duration and type of participation, description of the procedures, contact persons for the research including the chairs of the University of Windsor and Ryerson University Research Ethics Boards, voluntary nature of participation, and the right to withdraw without penalty.

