**4.9.3 Quantitative Measures**

The quantitative measures used in this study have been demonstrated to possess good reliability and validity, as well as documented associations with risky sexual behaviour23,51,52,59,60. It is anticipated that the entire protocol will take approximately 50 minutes to complete at each timepoint: baseline, post-intervention, and 3 months after the end of the intervention.

**Demographics Questionnaire.** Participants will complete a demographics questionnaire assessing age, ethnic/racial background, religious affiliation, educational level, living situation, marital/partner status, socioeconomic status, and sexual orientation.

**Primary Endpoint Variable: Unprotected Sexual Behaviour.** Participants will be asked to indicate their frequency of unprotected anal intercourse with HIV-negative or unknown HIV status partners in the past 3 months.

**Secondary Endpoints.** Secondary endpoints will also examine protected and unprotected 1) insertive and receptive anal intercourse with men, 2) anal and/or intercourse with women with and without a condom in the previous 3 months with partners who were HIV+, partners who were HIV-negative, and partners of unknown serostatus. Second, participants will be asked to indicate their number of HIV+ partners, HIV-negative partners, and partners of unknown serostatus in the previous 3 months. Third, participants will be asked if they had insertive or receptive anal intercourse or vaginal intercourse with their last sex partner, as well as their last partner’s serostatus.

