**4.10.3 Research Stage III – Data Entry and Analysis**

The study coordinator will oversee data management procedures established in study stage I once data collection has begun. Data entry and analysis will proceed until month 9 of Year 2 of the study. Statistical analysis will be conducted under the guidance of the quantitative psychologist of the study team, [name], who is well-trained in analyses of behavioural intervention data. Completed protocols will be stored in a locked file cabinet and only assigned participant identification numbers will appear on completed assessment materials to protect confidentiality. A data file will be created using SPSS or STATA into which coded data will be entered. If the primary endpoint is not normally distributed, it will be transformed using the formula [log10 (x +1)]82 to avoid violations of assumptions of normality in parametric analyses. If this does not sufficiently correct for positive skew or kurtosis, data will be dichotomized per standard convention in the HIV behavioural literature into presence or absence of unprotected sex with non-HIV+ partners in the past 3 months.

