**5.0. relevance and potential impact**

Despite the need for interventions that address increasing HIV diagnoses among MSM, higher rates of UAI among HIV+ versus HIV-negative MSM, and the barebacking phenomenon among MSM, there is a lack of interventions that specifically focus on HIV+ MSM, many of whom may not be motivated to use condoms during anal intercourse. The primary objective of the present study is to evaluate a small-group HIV prevention program for HIV+ MSM using motivational enhancement counselling to reduce sexual risk behaviour. An effective HIV prevention intervention for HIV+ MSM has the potential to make a significant difference in epidemiological trends in HIV in Canada.

The proposed study will provide data on the effect size of a small group-based motivational enhancement counselling behavioural intervention for HIV+ MSM. Although behavioural intervention research among primarily American samples of non-HIV+ MSM and HIV+ persons who are not exclusively MSM has documented effect sizes for HIV prevention interventions41, none have found a significant effect of an HIV prevention behavioural intervention for HIV+ MSM in Canada, nor have any studies examined the effect of a small-group based intervention using motivational enhancement counselling for HIV+ MSM. Armed with the data from the present study demonstrating the effect size of the intervention, the study team will then design and implement a randomized controlled trial to examine the efficacy of the intervention in Toronto and other sites serving HIV+ MSM in Canada.

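### The pre-post change in a single arm selected on its own primary endpoint is not the intervention's effect size, and should not be labelled or carried into the RCT as such

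*Protocol*

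**What the plan says.** - **Aim and use.** Section 3.0: "This Phase II trial will determine the effect size of the intervention". Section 1.0 makes the effect size the primary objective. Section 5.0 begins its account of the next step with "Armed with the data from the present study demonstrating the effect size of the intervention" and goes on to the design of a randomised trial.
- **Hypothesis.** Section 3.0: "the study intervention will result in reduced prevalence of unprotected anal intercourse (UAI) with partners who are HIV-negative or unknown serostatus".
- **Arms.** Section 4.2: "Participants will complete 6 sessions of a small-group sexual health intervention to reduce sexual risk behaviour". No control, wait-list or other comparison group is described. Section 4.4 analyses time as a within-subject factor.
- **Entry.** Section 4.3 admits those who "are HIV+ men who report UAI with a partner of HIV-negative or unknown HIV status in the past 3 months".
- **Primary endpoint.** Section 4.9.3: "frequency of unprotected anal intercourse with HIV-negative or unknown HIV status partners in the past 3 months". If a log transformation does not cure skewness, section 4.10.3 has it "dichotomized per standard convention in the HIV behavioural literature into presence or absence of unprotected sex with non-HIV+ partners in the past 3 months".
- **Source population.** Section 4.5 says that "about half of HIV+ men are likely to have had unprotected sex with a partner" of HIV-negative or unknown status. The same section then directs recruitment to venues where men who often have unprotected sex are over-represented.
- **Bias control.** Section 4.9.3 measures social desirability. Regression to the mean and time trend are not mentioned.

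**The concern.** The entry rule and the primary endpoint share the behaviour, the partner type and the length of recall, and baseline is taken at enrolment. Behaviour and its reporting fluctuate, so men picked because a 3-month window was positive will on average report less in a later window with no help from the intervention. With no comparison group, the analysis cannot separate this from an effect, or from changed reporting or a time trend.

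What is at stake is the trial's own headline number. Its stated purpose is to supply an effect size. If that number contains an unknown amount of regression, it looks better than the intervention is, and it goes forward under that name to the planning of the next trial.

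**Working it through.** **1. The plan's own figure.** Section 4.4 gives N=40 for a medium change at alpha 0.05 and power 0.80, and 7 × 6 = 42 enrolled. The variance components are not given, so the trajectory-model calculation cannot be rerun. As a guide, a two-sided paired t-test with 80% power detects 0.454 SD of change at n=40 and 0.443 SD at n=42; a conventional 0.5 SD needs 34. N=40 is plausible and not shown to be wrong. The effect sought is thus roughly 0.44-0.50 SD of the change score.

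**2. Fallback endpoint (any versus none), no intervention effect.** If a share p of the source population is positive in any window and the within-person correlation between windows is φ (assumed), the share of enrolled men still positive later is p + φ(1 − p). Baseline is 100%.

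| p | φ = 0.3 | φ = 0.5 | φ = 0.7 | φ = 0.9 |
|---|---|---|---|---|
| 0.30 (section 2.1) | 51% | 65% | 79% | 93% |
| 0.376 (section 1.0) | 56% | 69% | 81% | 94% |
| 0.50 (section 4.5) | 65% | 75% | 85% | 95% |

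The apparent fall is 5 to 49 percentage points. The 30% refers to a one-year window; the windows for the other two are not stated. Because change can go only one way, the exact paired test gives p = 2 × 0.5^k when k men are negative at follow-up: k = 5 gives 0.0625 and k = 6 (14% of 42) gives 0.031. At p = 0.50, the expected k is 42 × 0.05 = 2.1 for φ = 0.9 and 42 × 0.15 = 6.3 for φ = 0.7.

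**3. Latent-normal outcome, no effect.** Regression in baseline SD of those enrolled = (1 − r) × m/s, where m and s are the mean and SD of a standard normal above the entry cut, and r is the assumed test-retest correlation. At 50% eligible, m = 0.798 and s = 0.603, so r = 0.5 gives 0.5 × 0.798/0.603 = 0.66.

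| Share eligible | r = 0.5 | r = 0.7 | r = 0.8 |
|---|---|---|---|
| 37.6% | 0.92 | 0.55 | 0.37 |
| 50% | 0.66 | 0.40 | 0.26 |
| 80% (assumed) | 0.23 | 0.14 | 0.09 |
| 90% (assumed) | 0.12 | 0.07 | 0.05 |

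**4. Simulated counts, no effect.** This is closer to the actual endpoint: Poisson-lognormal counts, entry if the baseline count exceeds 0, change in log10(x+1), two-sided paired t-test at n=42. At prevalence 0.5, with log-rate SD 2.0 and a stable share of variance of 0.5, 0.7 or 0.9 (all assumed), the fall is 0.50, 0.39 or 0.27 baseline SD, and about 69%, 59% or 53% of trials are significant. At an assumed prevalence of 0.86-0.91, the fall is 0.05-0.12 SD with 7-14% significant. At 0.94-0.95, about 5-7% are significant. The nominal rate in the direction of a reduction is 2.5%.

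**5. Would an earlier window help?** In the same kind of no-effect simulation, follow-up minus a pre-enrolment window that was not used for selection differed from zero by at most about 0.005 SD. That contrast therefore removes the regression if behaviour is stable and recall is comparable. It does not remove reporting change or time trend.

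**The case against.** The strongest reply is that section 4.5 does not recruit from all HIV+ men. It goes to venues with many men at frequent risk, and section 2.3.3 describes such men as fairly consistent in this behaviour. Both facts reduce regression: in such a source the entry rule excludes few men and behaviour varies less. This stands. It moves the plausible size towards the low end, but does not remove the bias, because one reported event still suffices for entry. The prevalence at the venues is not given, so neither end of the range is established.

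Second, this is Phase II, efficacy is reserved for a later randomised trial, and section 4.9.2 gives improvement of the intervention as the goal of the evaluation. That is fair as to the study's role, but the effect size is this study's own primary objective. The causal wording of the hypothesis is not itself a fault; hypotheses are worded that way. Social desirability is measured, which is a partial check on reporting but not on regression.

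Two stronger readings are tempting. A reader might infer that the bias is about as large as the medium effect the trial is sized for. The protocol gives no within-person correlation, no count distribution and no number for medium, so this cannot be shown. A reader might also infer that the RCT will be underpowered. For illustration, a trial sized on d = 0.5 (63 per arm) would have about 29% power if half of that were regression, and 252 per arm would be needed. But section 5.0 says only that the trial will be designed with these data in hand, not that its sample size will be computed from the raw change, and section 4.11 foresees modifying the intervention first.

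**Conclusion.** The point holds as one of labelling and use. Selection on the endpoint in a single arm makes a fall without any effect the expected result, and the bias from selection favours the intervention; this follows from the design alone. Its size depends on assumptions: from about 0.05 baseline SD where source prevalence is 0.9 or more and behaviour is stable, to about 0.4-0.6 SD or more where prevalence is about 0.5 and behaviour is less stable. False significant reductions at N=42 correspondingly run from about 5% to over 50%. All these figures assume no intervention effect, no time trend and no reporting change. Should-fix: the study can be run as designed, but its main number cannot be read as named.

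**What to change.** 1. In sections 1.0, 3.0 and 5.0, state that the trial estimates uncontrolled within-person change, not the effect size of the intervention, and that this value will not be used unadjusted as the planning effect for the RCT.
2. Add one baseline item asking the same frequency for months 4-6 before enrolment, not used for eligibility. Report follow-up against that window as a sensitivity contrast beside the main one.
3. Do not also subtract an assumed amount of regression. The correlation needed is unknown, and applying it to the months 4-6 contrast would correct twice.

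Cost: a few sentences and one questionnaire item. The downside is poorer recall of the older window, which, if events are forgotten, biases this contrast against the intervention, and a less favourable headline. The single-arm community design stays as it is.
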